## 12 REGULATORY AND ETHICAL APPROVALS

### 12.1 Statement of Compliance

The trial will be carried out in accordance with Good Clinical Practice (ICH GCP) and the Declaration of Helsinki (1996).

### 12.2 UK Policy Framework for Health and Social Care Research Regulatory Approval

This trial falls within the remit of the EU Directive 2001/20/EC, transposed into UK law as the UK Statutory Instrument 2004 No 1031: Medicines for Human Use (Clinical Trials) Regulations 2004 as amended. This trial has been registered with the MHRA and has been granted a Clinical Trial Authorisation (CTA). The EudraCT reference is 2018-003893-29.

### 12.3 Ethical Considerations

The specific ethical issues relating to participation in this trial are considered to be:

**Informed consent in a paediatric population:** The appropriate adult providing consent on behalf of the minor participant will have an interview with the investigator, or a delegated member of the investigating team, during which opportunity will be given to understand the objectives, risks and inconveniences of the trial and the conditions under which it is to be conducted. They will be provided with written information and contact details of a member of the research team at the centre, from whom further information about the trial may be obtained, and will be made aware of their right to withdraw the child from the trial at any time without the child or family being subject to any detriment in the child's treatment. Children will receive information, according to their capacity of understanding, about the trial and its risks and benefits and their assent will be sought and obtained, where appropriate ( $\geq 7$  years old). Given the participatory approach of the qualitative sub-study, particular attention will be paid to ensuring that the children and parents/primary carers fully understand their involvement in the qualitative component. The approach and materials involved will be tailored, and wording used in the interview contexts will be developed, tailored and adjusted, in consultation with the PPI panel.

### 12.4 Ethical Approval

Prior to the trial being initiated at CTRC, a favourable opinion will be obtained from a REC and global governance approval from the Health Research Authority (HRA). Prior to opening a centre to recruitment, CTRC will ensure that local governance approval has been obtained: this will be "Capacity & Capability" Confirmation or R&D approval depending on the country of issue. A copy of localised versions of the participant/parent/appropriate adult information and consent/assent form should be forwarded to CTRC before the centre is initiated and patients recruited.

### 12.5 Protocol Deviation and Serious Breaches

A breach of the protocol or GCP is 'serious' if it meets the regulatory definition of being "likely to affect to a significant degree the safety or physical or mental integrity of the trial participants, or the scientific value of the trial". All serious breaches of GCP or protocol will be reported to the MHRA by KHP CTO and to REC by CTRC in an expedited manner.

If any persons involved in the conduct of the trial become aware of a potential serious breach, they must immediately report this to the CTRC who will in turn notify the co-sponsors. The co-sponsors will assess the breach and determine if it meets the criteria of a 'serious' breach of GCP or protocol and therefore requires expedited reporting to the MHRA and REC.

In determining whether or not the breach is likely to affect to a significant degree the safety, physical or mental integrity of participants, the co-sponsors may seek advice from medical expert members of the TMG and/or of the independent oversight committees (IDSMC and TSC). In determining whether or not the breach is likely to significantly affect the scientific value of the trial, the co-sponsors may seek advice from the trial statistician. However, the co-sponsors retain responsibility for the assessment of whether or not a breach meets the definition of 'serious' and is subject to expedited reporting to MHRA and REC.

Breaches confirmed as 'serious' will be reported to the MHRA by KHP CTO and to REC by CTRC within 7 days and notified to the TMG, IDSMC and TSC at their next meeting.

Any requests for additional information from the co-sponsors, TMG, TSC, IDSMC, REC or MHRA, will be promptly actioned by the relevant member(s) of the research team and open communication will be maintained to ensure appropriate corrective actions are taken and documented.

Incidence of protocol non-compliance are recorded as protocol deviations, the incidence of which is monitored and reported to trial oversight committees.

## **12.6 Trial Discontinuation**

In the event that the trial is discontinued, participants will be treated according to usual standard clinical care. The process for participants who withdraw early from trial treatment or from the trial completely is described in section 8.5.

## 13 DATA MANAGEMENT AND TRIAL MONITORING

Details of the monitoring to be carried out for the CASTLE trial are included in the CASTLE trial monitoring plan.

Trial oversight committees related to the monitoring of the trial are detailed in section 15.4.

### 13.1 Risk Assessment

A risk assessment is performed for each trial coordinated by the CTRC to determine the level and type of monitoring required for specific hazards. The type of trial monitoring should be specific to the individual trial and can take the form of routine on-site visits or central monitoring (with triggered on-site visits only).

In accordance with the CTRC processes, CASTLE will undergo a risk assessment, completed in partnership between:

- Representatives of the trial co-sponsors
- Chief Investigator
- Trial coordinator and supervising senior trial manager
- Trial statistician and supervising statistician
- CTRC Director

### 13.2 Source Documents

**Source data:** *All information in original records and certified copies of original records of clinical findings, observations, or other activities in a clinical trial necessary for the reconstruction and evaluation of the trial. Source data are contained in source documents (original records or certified copies; audio recordings; interview transcripts; drawings and diary entries). (ICH E6, 1.51).*

**Source documents:** *Original documents, data, and records (e.g., hospital records, clinical and office charts, laboratory notes, memoranda, participants diaries or evaluation checklists, pharmacy dispensing records, recorded data from automated instruments, copies or transcriptions certified after verification as being accurate copies, microfiches, photographic negatives, microfilm or magnetic media, x-rays, participant files, and records kept at the pharmacy, at the laboratories and at medico-technical departments involved in the clinical trial). (ICH E6, 1.52).*

In order to resolve possible discrepancies between information appearing in the CRF and any other patient related documents, it is important to know what constitutes the source document and therefore the source data for all information in the CRF.

The CRF will be considered the source document for data where no prior record exists and which is recorded directly in the CRF. A CASTLE source document list will be completed by each centre to confirm the source documents.

Date(s) of conducting informed consent (plus assent where appropriate and if sought/reason if not sought) process including date of provision of patient information, type and version of information sheets used, confirmation of full eligibility, randomisation number and the fact that the patient is participating in a clinical trial (including possible treatment arms) should be added to the patient's medical record chronologically.

## 13.3 Data Capture Methods

Clinical data capture will be in the form of paper copies of CRFs that will be returned as an on-going process from each centre to the CTRC. Patient/parent reported data will be collected directly on paper at each outpatient visit with the exception of CANTAB, which will be collected on iPads at the centre.

All data transferred from centres to CTRC will be pseudonymised and must be sent separately to documents containing identifiers (e.g. consent/assent forms containing names) in order to preserve pseudonymisation and maintain confidentiality.

Questionnaires – Patient and primary carer questionnaires completed on paper are a source document and **centres should securely** store them and retain a copy before mailing originals to CTRC at their earliest convenience after completion.

The CANTAB application will be clearly set up to ensure correct data entry and both the iPad and the application will be password protected. Subject data is only stored on the tablet until the testing session has finished and the iPad is connected to the internet. CANTAB data is then securely uploaded and stored securely online. A summary of data will be securely downloaded by authorised CTRC users, who will perform the analysis.

The contacts database will securely store personal and contact details for participants randomised to PBS and/or selected for actigraphy. This system will be linked to the randomisation system, detect which participants have been randomised to PBS and/or selected for actigraphy and alert the sleep team at Oxford Brookes University. For participants randomised to the PBS arm, the contacts database will also use the participant's details to create their personal online PBS account and email them their account details.

Actigraphy data will be obtained from the actigraphy watches by the sleep research team at Oxford Brookes University, who will then use the information recorded in the sleep logs collected by the parent/primary carer (with or without participant) to identify the appropriate periods for sleep analysis. Data will finally be transferred by secure electronic means to the CTRC.

The e-learning PBS user data directly collected online from parents will be securely stored at CTRC.

The qualitative sub-study will take place across three time points, and will use in-depth, semi-structured, face-to-face or remote interviews, and prioritization activities, with participants. Across all time points participants' (parents/primary carers and children) experiences of dialogue with clinicians about their concerns, and their decisions and choices will be explored. Interview questions and materials will be developed in consultation with PPI panel. All interviews will be audio recorded and transcribed. Audio recordings will be retained in a secure environment until transcripts have been finalised.

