### 7.5.2 Contacts Database

The 'contacts database', also called CASTLE Contact Management System, is a secure system hosted by the University of Liverpool designed to be used immediately after randomisation. The system sits between the randomisation system and the online PBS intervention and will collect the required personal and contact details from participants if they have:

- Been allocated to receive the PBS intervention

and/or

- Been selected for actigraphy (and consented to actigraphy)

The required details will be entered in the contacts database by the research team at site. A personal login username and password, provided by the CTRC, will be required to access the contacts database; designated research staff will be issued with their personal login and password upon completion of training in the use of the system. When all fields in the contacts database have been completed and submitted by the research staff at site, an email will be automatically generated and securely sent to:

- the primary carer of the participant, which will include a link to the PBS intervention online and log in details (if the participant is randomised to the PBS arm).

and/or

- the sleep research team at Oxford Brookes University to inform them that a participant has been added so they can view the address and contact the parent/primary carer to arrange the shipment of the actigraphs (if the participant is selected for actigraphy and has consented to this).

The system is password protected and accounts will only be generated for specific members of the sleep research team at Oxford Brookes University and CTRC members that need access to participant's details.

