## **7.6 Who is Blinded to Allocations**

Data analysts will be blinded after assignment to interventions by assignment of randomisation numbers to participants.

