#### 9.1.2 Randomised Sleep Intervention

At the same time as randomisation to carbamazepine, levetiracetam or active monitoring, participants will be randomised to a PBS intervention or no PBS intervention (standard care).

The PBS intervention is an e-learning package for parents/primary carers and children with epilepsy. The e-learning package will be referred to as COSI (CASTLE Online Sleep Intervention) in patient facing documents. Those randomised to receive the PBS intervention will receive an email directly from the contacts database that will contain a website link, access instructions and unique login details to access the sleep intervention program online (COSI). An email reminder will be sent to the parent/primary carer 3 days after randomisation if they have not accessed COSI.

The contacts database will also email the sleep research team at Oxford Brookes University to let them know that a new participant has been allocated to receive the PBS intervention.. If a parent/primary carer has not accessed COSI and therefore is not using the PBS intervention within 6

days of randomisation, the sleep team will get notified via email and will then give the parent/primary carer a reminder call.

When participants have been selected for actigraphy, the initial email with the COSI account details (username, password and link) will not be sent until day 12 after randomisation to allow enough time for parent/primary carer and participant to wear the actigraph before using the online sleep intervention. Due to this delayed start, the email reminder will be sent to the parent/primary carer 15 days after randomisation instead if they have not accessed COSI. Again, if the PBS intervention has not been used by day 18 after randomisation, the sleep team will get notified via email and will then give a reminder call to parents/primary carers.

After 3 months of account creation, parents/primary carers will receive an email informing them that an evaluation module has become available. If they do not complete the evaluation module within 6 days, the sleep team at Oxford Brookes will be notified and will then proceed to give parents/primary carers a reminder call.

Telephone numbers and email addresses are collected for all participants in the consent form and will be saved in the contacts database if they were allocated to the PBS arm or selected for actigraphy.

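### Nothing in the protocol keeps those who mark the actigraphy sleep periods from knowing the sleep allocation

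*Protocol*

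**What the plan says.** Four parts of the protocol bear on this.

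- **Allocation notices (9.1.2, 13.3).** "The contacts database will also email the sleep research team at Oxford Brookes University to let them know that a new participant has been allocated"; the arm meant is PBS. Section 13.3 adds that the contacts database, which is linked to the randomisation system, will "detect which participants have been randomised to PBS and/or selected for actigraphy and alert the sleep team at Oxford Brookes University".
- **Reminder calls (9.1.2).** In the actigraphy subset, "if the PBS intervention has not been used by day 18 after randomisation, the sleep team will get notified via email", and a call follows. Outside the subset the trigger is day 6. If the 3-month evaluation module is not completed within 6 days, "the sleep team at Oxford Brookes will be notified and will then proceed to give parents/primary carers a reminder call".
- **Scoring (13.3, 8.2.5.2).** The sleep team takes the data off the watches and is the party "who will then use the information recorded in the sleep logs collected by the parent/primary carer" to pick the periods for analysis. Transfer to the CTRC comes after that. The variables analysed are sleep latency, total sleep time and sleep efficiency.
- **Blinding (7.6).** The section consists of one sentence: "Data analysts will be blinded after assignment to interventions by assignment of randomisation numbers to participants". Actigraphy scorers are not mentioned.

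Two partial safeguards exist. Section 7.5.2 says that "accounts will only be generated for specific members of the sleep research team" and for CTRC members who need access. Section 13.5 says that actigraphy data are pseudo-anonymised.

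**The concern.** Choosing the analysis window is the step in actigraphy that needs human judgement. Where the log and the trace disagree, or the log is incomplete, somebody decides where the night starts and ends. That decision feeds into sleep latency and sleep efficiency, and can feed into total sleep time. A scorer who knows which families received the programme can resolve doubtful cases in its favour without intending to. Because this happens before transfer, blinding the CTRC analysts cannot undo it.

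The stake is the value of actigraphy as an objective measure. The trial is openly unblinded, and the CSHQ is completed by parents who know whether they were given the sleep programme. Actigraphy is the only sleep outcome that does not rest wholly on parental report, and section 8.2.5.2 lists the effect of the different treatments among its uses.

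**Working it through.** The plan states no figure that can be reproduced here. The check is a comparison of sections, followed by the counts and one assumed example.

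**1. Does the team learn the sleep allocation?** Yes. The email in 9.1.2 goes out for each new PBS participant and does not depend on the family's behaviour. The team is also told who has been selected for actigraphy (7.5.2, 8.2.5.2, 13.3). A participant selected for actigraphy with no PBS notice must be in standard care, so the team can know both sleep arms. The protocol does not say that it is told the drug allocation.

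**2. Does the team know who the participants are?** Yes. Under 8.2.5.2 it views name, address, telephone number and email in the contacts database, contacts the parent and ships the watches.

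**3. Does the same team make the scoring choice?** Yes, under 13.3, and before the data leave Oxford Brookes.

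**4. Does any provision separate the two roles?**

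- Section 7.6 covers data analysts only.
- The pseudonymisation in 13.5 applies to data collected by a team that also holds contact details and PBS notices. Nothing says the link is unavailable to scorers.
- The account restriction in 7.5.2 makes a division of tasks possible but does not require it.

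**5. Is the baseline recording protected by its timing?** No. Watches are sent after randomisation (7.5, 9.1.1.1), so every recording is made and scored after allocation.

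**6. How many dyads are affected?** From 8.2.5.2:

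- fitted: 6 subgroups × up to 15 = up to 90 dyads
- analysed: 6 subgroups × 10 = 60 dyads
- by sleep arm: 3 drug groups × 10 = 30 PBS and 30 standard care

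**7. What could a small shift in the window do?** This is an assumed night, not one from the documents: 600 minutes in bed and 540 asleep.

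- sleep efficiency as marked: 540/600 = 90.0%
- lights-out marked 10 minutes later: 540/(600 − 10) = 540/590 = 91.5%
- sleep latency falls by 10 minutes; total sleep time is unchanged in this example

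The recorded sleep is the same, yet two of the three summary variables look better. The 10 minutes are illustrative only. Nothing in the protocol indicates how large a real shift would be.

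**The case against.** Several points on the other side have force.

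- **The knowledge is shown for a team, not for individuals.** The few members with database accounts may not be the people who score. This stands. A reader might infer that the recordings are in fact scored with allocation known, and the text does not support that. It supports only that nothing prevents it.
- **The link to records is not fully spelled out.** A reader might assume that the team sees randomisation numbers in the contacts database. The protocol lists contact details there and does not mention numbers. The concern does not need them, since names together with PBS notices are enough.
- **The parent log anchors the window.** It records lights-out, subjective sleep times and when the watch was on or off, so the scorer is not free to place the marks anywhere. This stands and limits the room for bias. Judgement remains where the log is missing, implausible or at odds with the trace.
- **The parents who keep the logs are unblinded.** This too stands. Masked scoring does not touch that route. It removes a second, avoidable one.
- **The calls are conditional.** Only PBS families who have not used the programme or not finished the evaluation module are called. The allocation email, however, covers every PBS participant.
- **Actigraphy is an 'Other' objective in a subset, and 7.6 promises blinding of analysts only.** No stated commitment is broken. The protocol nowhere assigns actigraphy the job of validating the CSHQ result.
- **A scoring procedure outside the protocol could settle this.** It could, and none is shown. But the protocol itself chooses to fix who is blinded and who prepares these data, and as written those rules leave the gap open.

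**Conclusion.** The concern holds in a limited form. The team that receives every PBS allocation, and calls some PBS families, also selects the actigraphy sleep periods before the CTRC sees the data. No rule in the protocol keeps scorers from knowing the sleep allocation. What is affected is one 'Other' outcome, analysed in 60 dyads, 30 in each sleep arm.

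A reader might go further and conclude that the sleep result as a whole is compromised, or that up to 45 dyads per arm are at stake. Neither follows. The primary sleep outcome is the CSHQ, which does not pass through this step, and 45 per arm is the maximum fitted (3 × 15), not the number analysed.

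The size of any bias cannot be derived from the documents. The conclusion rests on two assumptions: that marking sleep periods leaves some discretion after the log has been consulted, and that no separate procedure already masks the scorers. It is a worthwhile, low-cost improvement that protects the trial's only objective sleep measure, and not a threat to the main results.

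**What to change.** Amend three sections so that they agree.

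- **8.2.5.2 and 13.3:** each recording and its sleep log carry a neutral code. Sleep periods are marked under that code by existing sleep-team members who hold no contacts-database account, receive no PBS notices and make no reminder calls. Scored files go to the CTRC before codes are linked to allocation.
- **7.6:** add actigraphy scorers to those blinded to the sleep allocation.

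The cost is relabelling files and dividing tasks within the current team, which the account restriction in 7.5.2 already permits. The team loses some flexibility in who handles the watches and who scores. The change does not remove bias that may enter through logs kept by unblinded parents, and the report should say so.

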## 13.4 Monitoring

### 13.4.1 Central Monitoring

Data received on CRFs at CTRC will be checked for missing or unusual values (range checks) and checked for consistency within participants over time. Any suspect data will be returned to the centre in the form of data queries. Data query forms will be produced at the CTRC from the trial database and sent either electronically or through the post to a named individual (as listed on the centre

delegation log). Centres will respond to the queries providing an explanation/resolution to the discrepancies and return the data query forms to CTRC. The forms will then be filed along with the appropriate CRFs and the appropriate corrections made on the database. There are a number of monitoring features in place at the CTRC to ensure reliability and validity of the trial data, to be detailed in the trial monitoring plan.

